#### Intervention adherence and compliance

Researchers will take the following measures to improve adherence to the intervention protocol: (1) sufficiently implementing informed consent, informing the potential benefits and risks, and instructing patients to fully understand the importance of taking medication according to the study protocol before participation (2); recording contact details of participants to keep in touch, including but not limited to mobile phone, QQ, WeChat, and email (3); highlighting the visit time in patient diary card; and (4) calling to remind the participants 1 day before a visit. At the final visit, patients will be requested to bring back the remaining drugs and packaging and be asked whether they take the drugs in the correct amount on time, whether they miss the medication, or whether they take fewer or more medications. All the information should be recorded in the original research medical records in a timely manner. Trial drug compliance will be calculated as the actual taken amount divided by the total scheduled amount.

### Outcome measures

#### Primary outcome

Cough resolution rate: proportion of patients whose cough is completely resolved after treatment.

The overall frequency, severity, and impact of cough will be evaluated using a patient self-rated cough symptom score (CSS) scale. CSS scale will be graded twice daily at two intervals: daytime (from 8:00 am to 8:00 pm) and nighttime (from 8:00 pm to 8:00 am), each scored from 0 to 3 points [16]. Cough resolution will be defined as both daytime and nighttime CSS scale reduced to 0 without relapse for two consecutive days.

#### Secondary outcomes

The following are the secondary outcomes:Change of bronchitis severity scores from baseline to post-treatment: Bronchitis severity score (BSS) is an observer-rated tool for assessing the severity of five major symptoms of AB including cough, sputum production, rales/rhonchi (auscultation), chest pain during coughing, and dyspnea, each rating from 0 to 4 points. The BSS is the sum of the five ratings ranging from 0 to 20 points [17].Cough relief rate: Cough relief will be defined as both daytime and nighttime CSS decreasing to 1 or less, or decreasing by 1 and lasting for two consecutive days. Cough relief rate will be the proportion of patients who achieve cough relief after treatment.Time to cough resolution: length of time at baseline to cough resolution: For example, the daytime and nighttime CSS on the patient’s diary cards on the 5th and 6th days are all 0 points, then the cough resolution time is recorded as “5 days.”Time to cough relief: Length of time at baseline to cough relief.Resolution rate of single TCM symptom.Combination medication use: Combination medication here will only include antibiotics, expectorants, and antitussives.Change of TCM syndrome score from baseline to post-treatment: Each TCM symptom will be graded (see Additional file 1). TCM syndrome score will be the sum of the main symptom score and all minor symptoms scores.Adverse events: Besides routine blood, urine, and stool tests and hepatic and renal functions, any unexpected symptom or sign during the treatment period will be recorded and analyzed.

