**Inclusion criteria**	
1. Diagnosis of acute bronchitis	
2. Phlegm-heat obstructing lungs syndrome in traditional Chinese medicine Zheng	
3. Total cough symptom score ≥ 4 points	
4. Expectoration in traditional Chinese medicine symptom score ≥ 6 points	
5. Bronchitis severity score ≥ 6 points	
6. Disease course within 72 h	
7. Aged 18 to 65 years old	
8. Voluntarily provide written and informed consent	

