### Sample size calculation

The sample size was calculated based on the comparison of cough resolution rate between the Tanreqing oral liquid group and the placebo group. According to the pilot study and expert consultations, the cough resolution rate for the Tanreqing oral liquid group and the placebo group was estimated as 80% and 40%, respectively, with a difference of 20% or higher considering clinically significant. According to the formula of $${n}_c=\frac{{\left({z}_{1-\alpha }+{z}_{1-\beta}\right)}^2}{{\left({\pi}_T-{\pi}_C-\Delta \right)}^2}\left[\frac{\pi_T\left(1-{\pi}_T\right)}{K}+{\pi}_C\left(1-{\pi}_C\right)\right]$$, where *π*_*T*_, *π*_*C*_ were the estimated cough resolution rate for the trial and placebo group of 0.8 and 0.4, respectively, Δ was the superior margin of 0.2, *α* of 0.025 was the one-sided 0.025 level of significance, *β* of 0.2 was the type II error, and the sample size of the placebo group was 63. According to the Tanreqing oral liquid group to placebo group ratio of 2:1, the sample size of the Tanreqing oral liquid group was 126.

According to regulatory requirements of a new 6th category oral drug of traditional Chinese medicine, the overall number of subjects in the Tanreqing oral liquid group should be no less than 300. Meanwhile, there are two independent clinical trials designed for different indications, i.e., AB and the common cold respectively to evaluate the efficacy and safety of Tanreqing oral liquid. Therefore, 300 subjects were divided into each indication equally to ensure that the overall subjects in Tanreqing oral liquid group would satisfy the regulatory requirement. Therefore, the total sample size was 225 (150/75 for the treatment and control group, respectively). Considering an expected post-randomization dropout rate of 20%, the sample size was set as 270, with 180 for Tanreqing oral liquid group and 90 for the placebo group.

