### Statistical analysis

The full analysis set (FAS) population will include all randomized participants who receive at least 20 mL trial medication and collect outcome data after treatment. It will be used to describe the analysis set which is as complete as possible and as close as possible to the intention-to-treat ideal of including all randomized participants. Per-protocol (PP) population will include all randomized patients who strictly follow the protocol. The safety set (SS) population will include all randomized participants who receive at least 20 mL trial medication and have safety evaluation data. Missing efficacy data will be imputed using the last observation carried forward method. Efficacy and safety analysis will be performed based on the FAS and PP population and SS population.

Statistical analysis will be performed using SAS 9.4 according to the statistical analysis plan. The primary outcome of cough resolution rate will be analyzed using the chi-squared or Fisher’s exact tests. Furthermore, logistic regression will be conducted to provide a risk ratio. For secondary outcomes, *t* test and nonparametric tests will be used for quantitative data, and chi-squared or Fisher’s exact tests will be used for qualitative data. A one-sided *P*-value of 0.025 or less will be considered statistically significant.

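### The changes in BSS and TCM syndrome score are to be compared without baseline adjustment, which gives up precision in two secondary outcomes

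*Protocol article*

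**What the plan says.** The Secondary outcomes section of the protocol article defines two symptom-scale outcomes as changes: "Change of bronchitis severity scores from baseline to post-treatment" and "Change of TCM syndrome score from baseline to post-treatment". On the first scale, "The BSS is the sum of the five ratings ranging from 0 to 20 points".

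The operative sentence is in the Statistical analysis section. For secondary outcomes, the t "test and nonparametric tests will be used for quantitative data". No covariate is named for them. The only regression mentioned is a logistic model supporting the primary outcome, cough resolution.

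Both baseline scores are available. The inclusion criteria require "Bronchitis severity score ≥ 6 points", so BSS is rated before treatment. The TCM score is also needed at baseline, because the change cannot be formed without it.

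**The concern.** Comparing mean change between arms is the same as regressing the post-treatment score on treatment with the baseline slope fixed at 1. If the true slope differs from 1, two things follow.

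- **Precision.** Part of the baseline variation stays in the change score as noise, and the confidence interval is wider than the data require.
- **Conditional accuracy.** If the arms differ by chance at baseline, the change score corrects for that difference by the wrong amount. With a slope below 1 it over-corrects.

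The nonparametric alternative does not solve this, because a rank test on the change does not adjust for baseline either.

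A slope below 1 is plausible here. The sample size section expects much recovery within seven days: cough resolution "was estimated as 80% and 40%, respectively". When a symptom falls to zero, its change is simply minus its baseline value and mostly reflects how ill the patient was at entry. Cough is only one of five BSS items, so this is an indication and not a measurement of the slope.

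**Working it through.** **Inputs from the article.** Allocation is 180 to 90. The significance level is "the one-sided 0.025 level of significance". For power, beta "of 0.2 was the type II error", that is 80%; this was set for the primary outcome and is used below only as a reference level.

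**Inputs not in the article (assumed).** Correlation r between baseline and post-treatment score: 0.2 to 0.7. Ratio L of follow-up SD to baseline SD: 1, with 0.75 and 1.5 as sensitivity values.

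**The plan's own figure.** None is stated for the change scores. The primary-outcome size does reproduce: (1.960 + 0.842)^2 / 0.2^2 x (0.16/2 + 0.24) = 62.8, so 63 placebo and 126 treated. Nothing below depends on it.

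**Step 1, variances.** In units of the baseline variance, per patient:
- change score: 1 + L^2 - 2rL
- ANCOVA: L^2(1 - r^2)
- difference: (1 - rL)^2, where rL is the slope

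The difference is never negative, so in large samples ANCOVA is never less precise. The two are equal when the slope is 1. With L = 1 the ratio is (1 - r^2) / [2(1 - r)] = (1 + r)/2.

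**Step 2, equal SDs (L = 1).** The equivalent N is 270 times the ratio: the number of patients with whom ANCOVA matches the change-score t test on 270. The last column takes an effect for which the t test has 80% power and computes Phi(2.802/sqrt(ratio) - 1.960).

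| r | Variance ratio | SE smaller by | Equivalent N | ANCOVA power |
|---|---|---|---|---|
| 0.2 | 0.60 | 23% | 162 | 95% |
| 0.3 | 0.65 | 19% | 175.5 | 94% |
| 0.5 | 0.75 | 13% | 202.5 | 90% |
| 0.7 | 0.85 | 8% | 229.5 | 86% |

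A simulation of 10,000 trials per setting at 180/90 gave variance ratios of 0.65, 0.76 and 0.86 for r = 0.3, 0.5 and 0.7. Both estimates were unbiased. One-sided type I error was 0.0246 to 0.0254 for the t test and 0.0243 to 0.0274 for ANCOVA.

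**Step 3, unequal SDs.** Variance ratio for r from 0.2 to 0.7:
- L = 0.75: 0.43 to 0.56
- L = 1.5: 0.82 to 1.00; the gain is nil at r = 1/1.5 = 0.67, where the slope is 1

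**Step 4, chance imbalance.** At 180/90 the baseline difference has an SD of sqrt(1/180 + 1/90) = 0.13 baseline SDs. The change score leaves (1 - slope) times the difference in the estimate. For a two-SE imbalance (0.26 SD) and a slope of 0.3, that is 0.7 x 0.26 = 0.18 SD. The SE of the change-score estimate at r = 0.3 and L = 1 is sqrt(1.4) x 0.129 = 0.15 SD.

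**The case against.** The strongest reply is that nothing here is an error. A comparison of change scores in a randomised trial is valid, the outcomes are secondary, and the article refers to a statistical analysis plan that is not shown and may add covariates. The first two points stand and set the weight of this comment. The third stands only in part: the unseen plan may adjust, but the article does not leave the method open. It names the tests, and they are unadjusted.

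It is also fair that the article offers nonparametric tests beside the t test, and that the (1 + r)/2 formula does not describe a rank test.

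A reader might infer more than the document supports:

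- **That the entry thresholds make the change score especially inefficient.** Under a linear model the opposite holds. Selecting on baseline shrinks the baseline variance but leaves the slope and residual variance unchanged, so the penalty (1 - slope)^2 x baseline variance shrinks. Example, assuming normal scores, equal SDs, r = 0.5 before selection and a cut at the mean: the ratio moves from 0.75 to 0.75/(0.75 + 0.25 x 0.363) = 0.89. The correlation falls to 0.33, and (1 + r)/2 would then wrongly give 0.66, because the SDs are no longer equal.
- **That regression to the mean biases the result.** It acts on both randomised arms and cancels in expectation.
- **That a baseline imbalance passes in full into the estimate, or that ANCOVA removes all imbalance.** Only (1 - slope) times the difference enters, and ANCOVA deals only with the score that is adjusted for.
- **That baseline cough score belongs in the cough-resolution model on the same grounds.** That is another outcome, and no calculation here supports it. If the total is the sum of two ratings of 0 to 3, an entry minimum of 4 leaves only the values 4, 5 and 6.

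**Conclusion.** The point holds as a minor one. The stated tests leave the two change outcomes unadjusted for baselines that are already recorded. The cost is precision and conditional accuracy in secondary outcomes. There is no bias over randomisations, type I error is not inflated, and the primary analysis is untouched.

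The variance reduction of 15% to 40% rests on equal SDs and r between 0.2 and 0.7. It should not be read as an estimate for this trial. The document supports only the direction: the gain could be larger if follow-up scores vary less than baseline scores, and close to nil if the slope is near 1. In large samples ANCOVA does not lose. At this size the loss is negligible even where there is nothing to gain: the finite-sample factor is 1 + 1/266, or 0.4%.

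**What to change.** In the Statistical analysis section, and in the analysis plan if it does not already say so, prespecify for BSS and TCM syndrome score:

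- ANCOVA of the post-treatment score with treatment, the matching baseline score and the randomisation stratification factor(s). Using the change as the dependent variable gives the same treatment estimate once baseline is in the model.
- The adjusted mean difference with its 95% CI as the reported result.
- The t test or rank test on the change as a sensitivity analysis.

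This needs no new data, visits or patients. The cost is wording, settled before unblinding so that the choice of adjustment cannot be questioned. If it counts as a significant change to the data analyses, the ethics section of the article requires a signed modification document and renewed ethics approval first.

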### Coordination and conduct of the trial

A multicenter trial coordination committee will be established and responsible for trial conduct. Data monitoring committee will not be established because (1) this trial will recruit AB participants and perform follow-up over a short period of 7 days, (2) pilot clinical observation found Tanreqing oral liquid was well tolerated and safety data from Tanreqing injection did not show any toxic potential in real-world cohorts [18], and (3) the primary outcome measure will be patients self-reported resolution of symptoms. Similarly, interim safety and efficacy analysis will not be conducted. An independent monitoring committee will conduct onsite monitoring monthly in accordance with the sponsor’s requirements and relevant regulations. An independent qualified auditor will randomly audit the trial to evaluate trial conduct and compliance with the protocol, good clinical practice, standard operating procedures, and the applicable regulations.

### Data collection and management

Research medical records will be the original documents in this trial, which will be properly kept by each study center. Trained researchers will collect baseline demographic parameters, outcome data, and other trial data at each visit. All participants will be instructed to grade their cough and TCM symptoms and record medication use and any unexpected condition on the daily diary card.

Plans to promote participant retention will be as follows: (1) instructing participants to fully understand the importance of study involvement and acknowledging their participations (2); recording contact details of participants to keep them in touch, including mobile phone, QQ, WeChat, and email (3); calling to remind participants one day before a scheduled visit (4); trying to re-contact or re-schedule at their convenient time in case of a missed visit (5); trying to collect outcome data when a participant withdraws from the study; and (6) providing a compensation of ¥600 after completing follow-up.

In this study, an electronic case report form (ECRF) created by electronic data acquisition system (EDC) will be used to collect and manage data online. The specific procedures and processes of data management will be standardized in data management plan to ensure real-time, traceability, consistency, accuracy, and integrity of data. The data entry personnel designated by each center will log into EDC, timely input related data at each visit. Data verification methods will include (1) on-site source data verification: a designated clinical supervisor will check the consistency of ECRF data and source data (2); system automatic logic verification: EDC will conduct automatic logic verification at the same time of data input and send out system questions in real time; and (3) manual verification: an independent data manager will manually check the data and issue manual queries if there is a problem. Researchers or researchers’ designated personnel will answer queries online in real time, and data administrators will review the answers, confirm to close, or issue questions again until the data is “clean.” At the end of the trial, the documents generated in the data management process will be saved and filed according to good clinical practice, requirements. Only data managers and statisticians will have access to exporting the final data. The sponsor and each center will store the ECRF in PDF format in a durable storage medium that cannot be edited.

### Adverse event reporting

An adverse event (AE) will be any unexpected or undesirable experience or condition throughout the treatment period, including clinical symptoms or signs irrelevant to AB, and abnormal laboratory findings. All AEs will be recorded in detail including specific presentation, occurrence date, degree, duration, the process, treatment measures, clinical outcome and prognosis. The causal relationship between an AE and trial drug will be timely judged according to the general guidelines for clinical research of new drugs of traditional Chinese medicine (November 2015) issued by China State Food and Drug Administration. A SAE will be defined as any adverse medical event that occurred at any dose at any time throughout the whole trial. SAEs may (1) result in death, (2) be life-threatening, (3) result in persistent or significant disability or incapacity, (4) require inpatients hospitalization or extend the length of hospital stay, or (5) be other important medical events in which the abovementioned conditions may occur without treatment. Any SAE must be reported to the Biomedical Ethics Committee of West China Hospital of Sichuan University, the sponsor, and China’s State Food and Drug Administration within 24 h.

### Sample size calculation

The sample size was calculated based on the comparison of cough resolution rate between the Tanreqing oral liquid group and the placebo group. According to the pilot study and expert consultations, the cough resolution rate for the Tanreqing oral liquid group and the placebo group was estimated as 80% and 40%, respectively, with a difference of 20% or higher considering clinically significant. According to the formula of $${n}_c=\frac{{\left({z}_{1-\alpha }+{z}_{1-\beta}\right)}^2}{{\left({\pi}_T-{\pi}_C-\Delta \right)}^2}\left[\frac{\pi_T\left(1-{\pi}_T\right)}{K}+{\pi}_C\left(1-{\pi}_C\right)\right]$$, where *π*_*T*_, *π*_*C*_ were the estimated cough resolution rate for the trial and placebo group of 0.8 and 0.4, respectively, Δ was the superior margin of 0.2, *α* of 0.025 was the one-sided 0.025 level of significance, *β* of 0.2 was the type II error, and the sample size of the placebo group was 63. According to the Tanreqing oral liquid group to placebo group ratio of 2:1, the sample size of the Tanreqing oral liquid group was 126.

According to regulatory requirements of a new 6th category oral drug of traditional Chinese medicine, the overall number of subjects in the Tanreqing oral liquid group should be no less than 300. Meanwhile, there are two independent clinical trials designed for different indications, i.e., AB and the common cold respectively to evaluate the efficacy and safety of Tanreqing oral liquid. Therefore, 300 subjects were divided into each indication equally to ensure that the overall subjects in Tanreqing oral liquid group would satisfy the regulatory requirement. Therefore, the total sample size was 225 (150/75 for the treatment and control group, respectively). Considering an expected post-randomization dropout rate of 20%, the sample size was set as 270, with 180 for Tanreqing oral liquid group and 90 for the placebo group.

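### The 20% dropout allowance is miscalculated: 270 randomized leaves 216 completing patients (144/72), not the 225 (150/75) that the protocol sets as its target

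*Protocol article*

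**What the plan says.** All the figures stand in the protocol article, section on sample size calculation.

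- **Efficacy requirement.** The resolution rates are given thus: "the cough resolution rate for the Tanreqing oral liquid group and the placebo group was estimated as 80% and 40%, respectively". Δ "was the superior margin of 0.2", α "of 0.025 was the one-sided 0.025 level of significance" and β "of 0.2 was the type II error". The placebo arm comes to 63, and "According to the Tanreqing oral liquid group to placebo group ratio of 2:1, the sample size of the Tanreqing oral liquid group was 126". The total is 189.
- **Regulatory increase.** For this drug category "the overall number of subjects in the Tanreqing oral liquid group should be no less than 300". Two trials, one in acute bronchitis and one in the common cold, share that number equally, so this trial's share is 150 on Tanreqing. Hence "the total sample size was 225 (150/75 for the treatment and control group, respectively").
- **Dropout allowance.** "Considering an expected post-randomization dropout rate of 20%, the sample size was set as 270", split 180 to Tanreqing and 90 to placebo. The inflation formula is not printed.

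**The concern.** The target, the dropout rate and the result are all printed, and they do not agree. A loss after randomization is a proportion of the patients randomized, so the number to randomize is the target divided by the proportion retained. The protocol's figure is instead the target plus 20% of the target, which always falls short of what the stated rate requires.

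The 225 is more than a loose cushion. Efficacy needed only 126/63. The rise to 150/75 has one stated purpose, to supply this trial's half of the regulatory 300, and the dropout allowance is then applied to that raised figure. If the allowance is too small, the target it is meant to protect is not secured under the protocol's own assumption. What is at stake is the accuracy of the stated dropout tolerance and, on one reading, the count of Tanreqing patients for the regulator.

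**Working it through.** **Inputs**, all from the section on sample size calculation: π_T = 0.80, π_C = 0.40, Δ = 0.20, one-sided α = 0.025, β = 0.20, K = 2, target 225 (150/75), dropout d = 0.20, stated size 270 (180/90).

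**1. Efficacy size, by the protocol's formula.**

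n_C = (1.960 + 0.8416)² / (0.80 − 0.40 − 0.20)² × [0.80 × 0.20/2 + 0.40 × 0.60]
= 7.849/0.04 × (0.08 + 0.24) = 62.79, rounded up to 63.

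Tanreqing: 2 × 63 = 126. Both stated figures are reproduced.

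**2. How 270 arises.** n × (1 + d): 225 × 1.2 = 270, 150 × 1.2 = 180, 75 × 1.2 = 90. All three printed figures are reproduced exactly.

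**3. What a 20% loss from those randomized requires.** n / (1 − d):

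| | Target | Target / 0.8 | Rounded up | Stated | Gap |
|---|---|---|---|---|---|
| Tanreqing | 150 | 187.5 | 188 | 180 | 8 |
| Placebo | 75 | 93.75 | 94 | 90 | 4 |
| Total | 225 | 281.25 | 282 | 270 | 12 |

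The gap is 12/282 = 4.3%, too large to be rounding.

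**4. What 270 leaves at 20% dropout.**

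- Total: 270 × 0.8 = 216, which is 9 below 225.
- Tanreqing: 180 × 0.8 = 144, which is 6 below 150.
- Placebo: 90 × 0.8 = 72, which is 3 below 75.

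**5. The dropout that 270 does cover.** For 150/75: 1 − 225/270 = 16.7%, the same in each arm (1 − 150/180 and 1 − 75/90). For the efficacy requirement of 126/63: 1 − 189/270 = 30%.

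**6. Effect on power.** By the same formula, power = Φ[0.20 / √(0.16/n_T + 0.24/n_C) − 1.960].

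| Tanreqing/placebo | Power |
|---|---|
| 126/63 (required) | 80.1% |
| 144/72 (270 less 20%) | 85.1% |
| 150/75 (target) | 86.5% |

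At 144/72, for example, the standard error is √(0.001111 + 0.003333) = 0.0667, and 0.20/0.0667 − 1.960 = 1.04, so power is 85.1%.

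**7. The regulatory count.** This trial's share is 150. If dropouts do not count, it supplies 144. The other trial's randomized size, inflation and dropout are not shown, so any pooled figure is an assumption. If that trial supplies exactly 150, the total is 144 + 150 = 294. If it is sized the same way and also loses 20%, the total is 2 × 144 = 288. If treated patients count whether or not they complete, up to 180 from this trial can count and its share of 150 need not be missed.

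**The case against.** The best defence is that nothing of substance is lost. The efficacy requirement is 126/63, and 270 meets it up to 30% dropout, so the primary comparison is safe. That stands. A reader might infer from a failed dropout allowance that the trial is underpowered. The protocol's own formula does not support that, since power at 144/72 is about 85% against the 80% planned.

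A second defence concerns the regulatory number. The text speaks only of the number of subjects in the Tanreqing group and does not say completers. Under the statistical analysis section, anyone who takes at least 20 mL and has safety data belongs to the safety set, so many patients who drop out would still be treated subjects with safety data. This also stands, and it rules out a firm statement that the 300 will be missed. It does not rescue the sentence on dropout. By inflating 150/75, the protocol treats dropouts as lost to that target. Either the inflation is miscalculated for its purpose, or the regulatory count does not need it.

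Third, a dropout is not automatically lost to analysis. The full analysis set keeps treated patients with post-treatment outcome data, missing efficacy data are carried forward, and the section on data collection and management plans to seek outcome data at withdrawal. The nine are therefore fewer completing patients than targeted, and it would be wrong to call them nine fewer evaluable patients.

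Last, one could say that multiplying by 1.2 is a common shortcut, or that a condensed article need not print its formula. Neither helps. The rate is described as a loss after randomization, and the three printed numbers disagree whatever formula lay behind them. No other section corrects them.

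**Conclusion.** The point holds as an arithmetic error in the stated dropout allowance. At the protocol's own 20%, 270 leaves 216 completing patients (144/72), 9 short of 225 (150/75). The figure consistent with 20% is 282 (188/94), and 270 covers 16.7%. This rests on reading the dropout rate as a share of those randomized, equal in the two arms, which is the natural sense of the text.

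The consequence is small. Power for the primary comparison stays above plan under the assumed rates of 80% and 40%. A shortfall of 6 against this trial's 150 arises only if dropouts do not count toward the regulatory number, which the protocol leaves open. A reader might go further and conclude that the minimum of 300 will be missed. That would need both this reading and facts about a common-cold trial that is not shown, so the totals of 294 and 288 are illustrations under assumptions and not findings.

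**What to change.** Keep 270 and correct the sentence. For example: 270 randomized patients (180/90) retain 150/75 if dropout is at most 16.7%; at 20% dropout, 144/72 complete, still above the 126/63 required for 80% power.

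As a clarification, add one sentence saying whether the regulatory 300 counts treated or completing subjects. If treated, say that the dropout allowance is not what secures this trial's 150. If completing, acknowledge that the share is met only up to 16.7% dropout.

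The cost is wording only, plus a slightly less favourable stated tolerance. No extra patients are needed. That suits the trial's position: the allocation numbers run from 001 to 270 (section on randomization and blinding), nine centres are to recruit 30 patients each (section on patient population and setting), and recruitment began on 30 November 2020 (trial status).
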